There will be two treatment groups: (i) test intervention, and (ii) comparator.

1. Treatment group: Will receive four capsules of vitamin A placebo orally (2 capsules for children aged <12 months) on the day of enrollment plus an oral dose of 5000 IU of vitamin A (in the form of multivitamin drops), and the same oral dose of vitamin A for the next 14 days i.e. throughout their entire nutrition rehabilitation phase in the hospital.
2. Comparator group: Will receive oral mega dose (4 capsules of vitamin A, each containing 50,000 IU i.e. a total of 200,000 IU; 2 capsules for children aged <12 months i.e. a total of 100,000 IU) plus an oral dose of 5000 IU of vitamin A (in the form of multivitamin drops), and the same oral dose of vitamin A for the next 14 days i.e. throughout their entire nutrition rehabilitation phase in the hospital.

A local pharmacutical company (Drug International, Bangladesh) will prepare and supply vitamin A capsules and placebo for the study. One of the investigators will administer the study interventions to the participating children following the randomization schedule at a fixed time of each day, and the date and time of actual administration will be recorded. Randomization will be done by an experienced scientist, not involved in the study in any way, using a block randomization method with variable sizes of blocks between 2 to 6.

Sample size

The sample size of this study has been estimated on expected proportions of clinical success in two groups. Earlier studies have observed 69% and 65% clinical recovery among children suffering from shigellosis and cholera respectively [53, 54], and 60% for pneumonia (personal communication with [name], Kamlapur field site of ICDDR,B) within 48 hours when treated with an effective antimicrobial agent. We assume that the recovery rate would remain same (i.e. 70%) in the high followed by low dose vitamin A group and there would be 15% increase in the rate i.e. 85% in the low dose vitamin A group. Considering 80% power at 5% significance the sample size is estimated as follows:

N = P1 (100-P1) + P2 (100-P2)  F (  ) where P1= 70% and P2 = 85%.

(P1- P2)2

= 118.  = 7.84

Thus the required sample size is 118 in each group, and with an anticipated dropout rate of around 10% the sample size will be 130 children in each of the two treatment groups i.e. a total of 260 children.

Patient recruitment, Clinical and Laboratory Assessments

1. **Patient recruitment**

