   1. Children will be screened for recruitment between 9 am to 4 pm everyday. A trained research assistant will initially screen them. After explaining the study including its aims, procedures, interventions and their possible risks and benefits, rights to refuse participation and withdrawal of consent during study, and confidential handling of information the parents/guardians would require to give consent to enroll their children. The same research assistant will then perform anthropometric measurements including height, weight and mid upper arm circumference, and calculate weight for age, height for age and weight for height percentiles taking National Center for Health Statistics (NCHS) median as the standard. Z-scores will be computed and children with weight for height Z-score less than 3 will be enrolled in the study .
   2. Final enrollment: After rehydration, children will be re-weighed, and final enrollment will be done if weight for height Z-score less than 3 .
2. **Clinical Assessments**
   1. Research assistant will collect the demographic and other data using a pre-designed clinical record form (CRF).
   2. One of the investigators will obtain pertinent medical history and perform through physical examination, and also ensure that the children meet eligibility criteria. All information would be recorded on a pre-designed and pre-tested case report form (CRF).
   3. Randomization: Patient will be randomly assigned to either of the two interventions based on a computer generated randomization table.
   4. During hospitalization data will be collected on the outcome variables as well as relevant clinical information including type and severity of diarrhoea and pneumonia.
   5. All the patients will receive standard treatment as per the hospital’s guidelines.
3. Laboratory assays
   1. **Blood test**s: Blood for retinol and RBP, glucose, complete blood count, serum electrolytes, total protein, albumin and, as measures of infection status, pre-albumin and C-reactive protein (CRP) will be measured after randomization on the admission day. Serum retinol and RBP will also be measured on study day-3 and 15. Any other heamatological test will be repeated if only clinically indicated. . Approximately 3.0 ml of venous blood will be adequate to perform all of the tests.

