**Data Analysis:**

Data will be entered onto personal computer using SPSS statistical package and statistical analyses will be performed using the same program, and z- scores will be determined using Epi Info 2001. Normally distributed continuous variables will be compared by t-test for normally distributed data and Mann Whitney U test will be used for data that are not normally distributed. Time to recovery would be compared by log rank test (Kaplan Mayer survival analysis). Two by two tables will be constructed to relate the findings of discrete variable such as chest X-ray findings of pneumonia (present or absent) and Fisher’s exact test would be performed where indicated. Statistical significance will be set at 5% level.

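### The planned comparisons of recovery ignore how ill each child was at entry; adjusting for values recorded before randomisation would cost almost nothing and may gain some power

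*Protocol*

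**What the plan says.** All references are to the protocol.

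- **Time to recovery** (Data Analysis): "Time to recovery would be compared by log rank test (Kaplan Mayer survival analysis"). No strata or covariates are named.
- **Binary data** (Data Analysis): two-by-two tables, and "Fisher’s exact test would be performed where indicated". The example given is a chest X-ray finding; the primary outcomes are not mentioned there. No regression model appears in the section.
- **Primary outcomes** (Primary outcome; Clinical success): resolution of diarrhoea and resolution of ALRI, with success for each defined as yes or no within 48 hours of effective therapy.
- **Randomisation** (Study Interventions): "using a block randomization method with variable sizes of blocks between 2 to 6", with no stratification factor.
- **Sample size**: "Considering 80% power at 5% significance the sample size is estimated as follows", with a two-proportion formula "where P1= 70% and P2 = 85"%, giving 118 per group and 130 after about 10% dropout.
- **Illness at entry**: Final inclusion in the study has the diagnosis (diarrhoea, ALRI/pneumonia or both) made before the child is enrolled. Clinical Assessments lists an investigator's history and physical examination before the randomisation step. After that step it lists data gathered during the hospital stay, including "relevant clinical information including type and severity of diarrhoea and pneumonia".

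**The concern.** The children enter with different illnesses (cholera, shigellosis, other diarrhoea, pneumonia, severe pneumonia) and probably with different severity. If severity at entry strongly predicts recovery by 48 hours, an unadjusted comparison leaves that variation in the error term. A chance difference in severity between the arms then also stays in the estimate, because neither the randomisation nor the analysis deals with it.

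The calculated sample size has little slack, so a few points of power matter. In a log-rank test, leaving out a strong predictor also pulls the overall hazard ratio towards 1. The information needed to adjust comes largely from assessments the protocol already schedules, so the gain, whatever its size, needs little or no extra data collection.

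**Working it through.** **1. The plan's own figure.** Inputs from Sample size: 70%, 85%, 80% power, 5% significance, multiplier 7.84 = (1.96 + 0.84)², which implies a two-sided test.

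n = 7.84 × (70×30 + 85×15) / 15² = 7.84 × 3375 / 225 = 117.6, so 118 per group. 118 × 1.1 = 129.8, so 130. Both figures reproduce.

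**2. Power of the unadjusted comparison.** SE = √[(0.21 + 0.1275)/118] = 0.0535. Power = Φ(0.15/0.0535 − 1.96) = 80.1%. The pooled formula gives 79% at 118 and 83% at 130. If Fisher's exact test were used throughout, exact power at 118 would be 75.4%. The trial is sized for an unadjusted comparison, and that comparison delivers about what was planned.

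**3. Illness type alone.** The only prognostic figures in the protocol are these: "Earlier studies have observed 69% and 65% clinical recovery among children suffering from shigellosis and cholera respectively", and 60% for pneumonia. With equal weights the mean is 0.647 and the between-type variance is 0.00136. R² = 0.00136 / (0.647 × 0.353) = 0.006, which is negligible.

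**4. Severity, binary outcome.** The protocol gives no figure for how strongly severity predicts recovery, so it is assumed over a range. Set-up: 118 per arm, marginal rates 70% v 85%, two equal severity groups (three equal groups for the illness-type row), 40,000 simulated trials. The unadjusted chi-square test is compared with a Cochran-Mantel-Haenszel test stratified by group.

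| Prognostic factor | Unadjusted | Stratified |
|---|---|---|
| none | 79.7% | 79.4% |
| illness type, spaced as 69/65/60% | 80.1% | 79.8% |
| severity OR 2 (assumed) | 79.8% | 80.3% |
| severity OR 4 (assumed) | 79.6% | 82.1% |
| severity OR 8 (assumed) | 80.0% | 85.1% |
| severity OR 16 (assumed) | 80.0% | 87.6% |

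Simulated type I error of the stratified test was 5.0% to 5.2%.

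**5. Severity, time to recovery.** 118 per arm, exponential times, two equal severity groups, 4,000 simulated trials. The treatment hazard ratio within strata is 1.44, chosen to give about 80% power.

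| Severity hazard ratio (assumed) | Unstratified log-rank | Stratified log-rank |
|---|---|---|
| 1 | 78.3% | 77.7% |
| 1.5 | 76.3% | 78.4% |
| 2 | 71.7% | 78.1% |
| 3 | 62.8% | 78.1% |
| 4 | 58.7% | 78.8% |

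If the hazards are instead set so that 70% v 85% have recovered at 48 hours, the unstratified test already has 93% to 97% power, and stratifying changes it by -1 to +4 points.

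**6. Number of children per outcome.** Each primary outcome can apply only to children who enter with that illness, and the protocol does not give the split. If only 59 or 83 per arm were evaluable for one outcome (assumed), power at a severity OR of 4 would go from 51.2% to 52.5%, or from 64.8% to 67.3%. The figures at 118 per group are therefore illustrative.

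**The case against.** Several objections stand and limit the point.

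- **An unadjusted analysis of a randomised trial is valid.** Chance imbalance is not bias, and the sample size was calculated for this kind of comparison. A reader might infer that the plan throws away power it had counted on. Step 2 shows that it does not.
- **The use of two-by-two tables for the primary outcomes is not stated.** The only example is chest X-ray. The reading is still a fair one: success is binary, the sample size compares two proportions, and the section offers no other binary method. The log-rank sentence is explicit.
- **The gain is unquantified in the protocol.** A reader might take a correlation of 0.5 between severity and outcome and conclude that adjustment adds about 10 points (R² 0.25 in the formula of step 2 gives 89.9%). The documents do not support that strength, and even an odds ratio of 16 reaches only 87.6% in simulation.
- **The sentence on type and severity is not about baseline data.** It refers to the hospital stay. Only values fixed before randomisation may be used, and the protocol does not establish that every candidate covariate is recorded by then.
- **Restricting each outcome to children with that illness** already removes part of the variation in case mix.

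The objection that this should simply be left to a statistical analysis plan has some force, since such a plan could add adjustment. But the protocol does fix its methods by name, and the stratified version is a specific improvement on what it names.

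**Conclusion.** The point holds as a conditional efficiency gain. The protocol names an unstratified log-rank test and, for binary data, only unadjusted tables; its randomisation names no strata. The planned analysis is not wrong and meets its stated power.

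The benefit of adjusting rests entirely on the assumed prognostic strength of entry severity. It is nil at the protocol's own illness-type rates, small at moderate assumed strength, and material only if severity is a strong predictor. The largest simulated gains, 15 to 20 points for the log-rank test, need a severity hazard ratio of 3 to 4 and a treatment effect smaller than the one planned.

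The sizes also assume two equal severity groups and 118 evaluable children per arm. The binary figures come from a stratified test, so they only approximate what a regression on the same covariates would give. The case for the change is that the possible gain clearly outweighs the cost.

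**What to change.** In Data Analysis, state the following:

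- Analyse each 48-hour primary outcome, among children who enter with that illness, by logistic regression on arm plus a few covariates recorded before randomisation. For both outcomes, include presence of the other illness. For diarrhoea, add entry stool frequency or type. For ALRI, add entry respiratory rate and severe or non-severe pneumonia.
- Report the result as a covariate-standardised risk difference with its 95% confidence interval.
- Stratify the log-rank test by the same entry severity groups.
- Keep the two-by-two table as the supporting, unadjusted result.

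**Cost.** This is a change of analysis wording. The case report form should be checked to confirm that these values are recorded before randomisation, and the covariates and severity groups must be fixed before unblinding. If severity turns out not to be prognostic, the loss is below 1 point of power (0.3 points for the binary outcome and 0.6 to 0.8 for the log-rank test in the simulations). Keep the covariates few, because each outcome may have well under 118 children per arm.

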**Ethical Assurance for Protection of Human Rights**

Describe in the space provided the justifications for conducting this research in human subjects. If the study needs observations on sick individuals, provide sufficient reasons for using them. Indicate how subject’s rights are protected and if there is any benefit or risk to each subject of the study.

**Justifications for conducting this research in human subjects**

Vitamin A deficiency is a major nutritional problem in developing countries including Bangladesh, and under-five children, particularly malnourished children are at higher risk. ALRI/pneumonia and diarrhoea are the two most common illnesses of under-five children. The beneficial role of high dose vitamin A supplementation, as an adjunct therapy in the treatment of diarrhea, has been documented in different studies. However, high dose vitamin A supplementation did not produce any beneficial effect on recovery from ALRI in well-nourished children with adequate stores, rather it increased the incidence of ALRI. WHO estimated that the lives of one million children could be saved globally each year through high dose supplementation of vitamin A. The results of five large trials in Asia have observed 20-30% drops in deaths from diarrhoeal diseases and pneumonia, and about one-third reduction in clinic attendance rate, hospital admissions and morbidity among vitamin A supplemented children. However, other studies have observed higher incidences of adverse events among malnourished children receiving high dose of vitamin A supplementation. The proposed study will examine if daily administration of a low dose of vitamin A produces similar effect on disease morbidity and lesser incidence of adverse events as compared to children receiving high dose vitamin A followed by daily administration of a low dose of vitamin A.

##### Protection of human rights

The intent of the research program, the study protocol, and the informed consent form to be used in the study will be submitted to the Ethical Review Committee of ICDDR, B and the study would be initiated only after receiving approval of the Committee.

**Informed Consent**

Written informed consent will be obtained from parent/guardians of each patient, in presence of a witness, before they can be enrolled in the study. It would be the responsibility of the investigators to obtain valid written informed consent from the parent/guardian after adequate explanation of the aims, methods, anticipated benefits and potential hazards of the study. The investigator must also explain to the parents/guardians that they are completely free to refuse to participation of their children in the study and also withdraw them from the study at any time during the study without showing any reason and without affecting their further treatment at the hospital for the current illness as well as in future. Parents/guardians will indicate their consent by signing the consent form or by putting their left thumb impressions (those who are unable to write), along with the date.

**Dissemination and Use of Findings**

Describe explicitly the plans for disseminating the accomplished results. Describe what type of publication is anticipated: working papers, internal (institutional) publication, international publications, international conferences and agencies, workshops etc. Mention if the project is linked to the Government of Bangladesh through a training programme.

The findings of the study will disseminated as follows:

1. Presentation(s) at Centre’s Scientific Forum (CSF), ICDDR, B for dissemination amongst Centre scientists.
2. Publication in peer-reviewed international medical journal.

**Collaborative Arrangements**

Describe briefly if this study involves any scientific, administrative, fiscal, or programmatic arrangements with other national or international organizations or individuals. Indicate the nature and extent of collaboration and include a letter of agreement between the applicant or his/her organization and the collaborating organization. **(DO NOT EXCEED ONE PAGE)**

This study will be conducted in collaboration with Khulna Medical College.

**APPENDIX**
